**Table 1 Tab1:**
[figure not shown]
Schedule of enrolment, interventions, and assessments

*BFI* Brief Fatigue Inventory, *FACT-F* Functional Assessment of Cancer Therapy-Fatigue, *EORTC QLQ-C30* European Organization for Research and Treatment of Cancer Quality of Life Questionnaire, *MoCA* Montreal Cognitive Assessment, *CHDE* Questionnaire for Cold-Heat & Deficiency-Excess Patternization

^a^The blinding and credibility tests will be performed only for the moxibustion and sham moxibustion groups

^b^The laboratory test includes complete blood count and differential count, absolute neutrophil count, aspartate aminotransferase, alanine aminotransferase, total bilirubin, gamma-glutamyl transferase, blood urea nitrogen, creatinine, albumin, glucose, hemoglobin A1c, erythrocyte sedimentation rate, C-reactive protein, thyroid-stimulating hormone, free thyroxine, and human chorionic gonadotropin urine test (only for women in their childbearing years at the screening visit)

### Outcome measurements

The following outcome measures will be assessed by assessors blinded to the group allocations.

#### Primary outcome measure

The mean change in average BFI scores from baseline to the end of the 8-week intervention will be the primary outcome measure of the study. The BFI is a questionnaire composed of 9 questions related to the degree of fatigue and the level of daily life interference caused by the fatigue [33]. Zero to ten points are assigned to each question (0 = no fatigue or no interference; 10 = the most severe level of fatigue or complete interference). The level of the fatigue can be grouped into three categories according to the average BFI score: 1–3 (mild), 4–6 (moderate), 7–10 (severe) [33].

#### Secondary outcome measures

The secondary outcome measures will include changes in average BFI scores from baseline to week 5 and week 13 and changes in the Functional Assessment of Cancer Therapy-Fatigue (FACT-F) scores, European Organization for Research and Treatment of Cancer Quality of Life Questionnaire C-30 (EORTC QLQ) scores, and Montreal Cognitive Assessment (MoCA) scores from the baseline to weeks 5, 9, and 13.

### FACT-F

The Functional Assessment of Cancer Therapy-General (FACT-G) is an assessment tool used to evaluate various functions in the daily lives of cancer patients [34]. It is comprised of 27 items in 4 domains: physical well-being, social/family well-being, emotional well-being, and functional well-being. The FACT-F is a combined questionnaire of the FACT-G plus a fatigue subscale including 13 items focused on fatigue and its related symptoms [34]. Using the FACT-F, diverse aspects of the life and the fatigue of cancer patients can be comprehensively assessed.

### EORTC QLQ C-30

The EORTC QLQ C-30 was devised by the European Organization for Research and Treatment of Cancer (EORTC) to assess the QOL of cancer patients [35]. It includes 30 questions across the three domains of global health status/QOL, function scale and symptom scale. A variety of modules for specific cancer sites have been developed [35], although this study will adopt only the general version.

### MoCA

It is known that many patients undergoing cancer treatment suffer from cognitive decline, and fatigue can affect the cognitive function of cancer patients [36]. The MoCA will be used in this study to evaluate the level of cognition of patients. This assessment tool was developed to screen for mild cognitive impairment, a transitional phase characterized by the cognitive changes that occur between early and normal dementia [37]. In this study, the MoCA will be used to detect patients with mild cognitive impairment and to assess changes in cognitive function.

#### Safety outcomes

The participants will be instructed to voluntarily report all AEs that occurred during the trial. The investigators will determine whether the participants experienced any AEs via inquiries at each visit and checking for changes in laboratory tests from baseline to week 9. The laboratory tests will include complete blood count, differential count, absolute neutrophil count, aspartate aminotransferase, alanine aminotransferase, total bilirubin, gamma-glutamyl transferase, blood urea nitrogen, creatinine, albumin, glucose, hemoglobin A1c, erythrocyte sedimentation rate, CRP, thyroid-stimulating hormone, free thyroxine, and human chorionic gonadotropin urine test (only for women in their childbearing years at screening visit). All AEs identified during the trial will be recorded in the clinical record form.

The severity of AEs will be classified into five grades according to the common terminology criteria for AEs (CTCAE, version 4.0) developed by the National Cancer Institute as follows: mild, moderate, severe, life-threatening, or death [38]. In cases for which the CTCAE is not applicable, Spilker’s three level criteria will be used, and the AE will be classified into one of the three levels: mild, moderate, and severe [39].

A causal relationship between an AE and the moxibustion treatment provided in this study will be evaluated based on factors such as the temporal relationship, combined therapy, and underlying diseases, etc. The result of the causal relationship assessment will be categorized to one of the following six criteria: definitely related, probably related, possibly related, probably not related, definitely not related, or unknown.

#### Blinding test and credibility test

A blinding test will be conducted for the participants of the moxibustion group and the sham moxibustion group. Assessors who were not involved in the treatment procedure will administer the blind test questionnaire to the participants in these two groups after the first and last treatments of the trial. In the questionnaire, the participants will be asked to answer whether they think they had received real moxibustion, sham moxibustion, or that they had no idea. The result of this test will reveal whether patient blinding was successfully maintained in the trial.

Another questionnaire to evaluate the credibility of the intervention and the patient blinding will be provided to the participants of the two groups at the same time points. The credibility test is composed of four questions asking if the participant felt that the treatment could alleviate their fatigue, if they would recommend the treatment to a friend suffering from a similar complaint, if the treatment seems logical to them, and if the treatment could successfully alleviate other complaints. The result of the test will show the participants’ expectations and confidence in the moxibustion treatment performed in this trial ranging from 0 (very low confidence) to 6 (very high confidence) [40].

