### Blinding

Practitioners cannot be blinded because of the unique nature of moxibustion treatment. Although the subjects of the usual care group will be able to determine which group they are allocated to, the participants in the moxibustion and sham moxibustion groups will be blinded. To assess whether the patient-blinding was successfully achieved among the moxibustion group and sham moxibustion group, the subjects of these two groups will undergo a blinding test and a credibility test after the first and final treatment. Outcomes will be assessed by researchers who are not involved in the intervention procedure. Thus, the assessors will be blinded to all three groups, while the participants will be blinded in only the moxibustion and sham moxibustion groups.

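### Assessors are said to be blinded to all three groups, yet assessors described in the same way give a questionnaire that only the two device arms receive

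*Protocol article*

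**What the plan says.** Three places in the protocol article make the blinding claim. The Blinding section defines the assessors by one attribute: "Outcomes will be assessed by researchers who are not involved in the intervention procedure". It then draws the conclusion: "Thus, the assessors will be blinded to all three groups". The Outcome measurements section repeats it: "The following outcome measures will be assessed by assessors blinded to the group allocations". The Abstract also describes the assessments at baseline and weeks 5, 9 and 13 as made by blinded assessors.

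The section on the blinding and credibility tests then states that assessors who took no part in treatment "will administer the blind test questionnaire to the participants in these two groups after the first and last treatments of the trial". The two groups are moxibustion and sham. The questionnaire asks whether the participant believes the treatment was real moxibustion or sham, or has no idea. A footnote to Table 1 confirms the restriction: "The blinding and credibility tests will be performed only for the moxibustion and sham moxibustion groups".

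**The concern.** A form that asks whether a treatment was real or sham makes sense only for someone who had a device applied. Whoever gives it to a participant therefore knows that this participant is not in usual care. If that person also assesses the participant's outcomes, the blinding claim is undone by a step that the plan itself prescribes.

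The comparison affected is moxibustion versus usual care. Under Statistical analysis this is the first hypothesis in the fixed sequence, and the sham comparison is tested only if it is rejected. In this comparison the practitioners are unblinded and the usual care participants know their group, so blinded assessment is the main safeguard left during data collection. The Discussion acknowledges incomplete blinding of participants but does not mention that assessors might learn the arm. A report repeating the claim of blinding to all three groups could then be wrong without anyone having departed from the protocol.

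**Working it through.** The article gives no figure that depends on this point, so the check sets its statements side by side.

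1. **Who assesses outcomes.** Blinding section: researchers who take no part in the intervention. Blinding to all three groups is inferred from that alone.

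2. **Who gives the blinding questionnaire.** Section on the blinding and credibility tests: assessors who took no part in treatment. The noun is the same and the qualifier is essentially the same. No section shown separates the two roles. None says that the form is returned sealed or that outcome assessors are kept from it.

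3. **Who receives it.** Moxibustion and sham only, stated in that section and again in the Table 1 footnote. With 96 participants allocated 1:1:1, each arm has 96 / 3 = 32. The form therefore goes to 2 × 32 = 64 participants, and 96 − 64 = 32 never get it.

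4. **When.** First after treatment 1, and again after the last treatment. The section on the study schedule takes baseline before the first intervention, then assesses at weeks 5, 9 and 13. Baseline is therefore untouched, and all three later assessments, including the primary one at week 9, come after the first use of the form.

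5. **What giving the form reveals.** Both device arms get the same form at the same times, so giving it separates device from no device and does not separate moxibustion from sham.

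| Comparison | Does giving the form reveal the arm? |
|---|---|
| Moxibustion vs usual care (tested first) | Yes, if the same assessors do both tasks |
| Moxibustion vs sham (tested second; basis of the sample size) | No |

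6. **Which outcomes are exposed.** The BFI is described as a questionnaire on the patient's own fatigue and its interference with daily life. An assessor's knowledge can reach it only through the way the form is presented or help is given. The MoCA section does not say who administers or scores that test. If an assessor scores it, knowledge of the arm has a more direct route to the score.

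**The case against.** The strongest reply is that the article never says the same individuals do both tasks. Three centres take part, staffing is not described, and a journal article may leave to the full protocol who hands out which form. This stands as a limit, and the point is therefore conditional. It does not remove the point, because the article is not merely silent. It infers blinding to all three groups from one attribute and then gives that same attribute to the people who handle a form that reveals the arm.

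A second reply is that the effect on the primary outcome is small. The BFI is the patient's own report, and usual care participants already know their group, which the article discloses. This also stands: the extra bias from the assessor's knowledge is probably modest.

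A reader might infer more than the text supports, in four ways:

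- **That assessor blinding is lost outright.** This needs the same people in both roles, which the wording suggests but does not state.
- **That assessors see each participant's guess of real or sham.** The article does not say whether the form is read aloud, self-completed or sealed, and a guess is not the allocation in any case.
- **That all 96 participants are revealed at every later visit.** The 64 is a count of those due to receive the form. Identifying the other 32 by default needs an assessor who knows which participants at the site had the form and who remembers it weeks later.
- **That the MoCA is certainly biased.** Scoring by an assessor is an assumption, and the MoCA is a secondary outcome that plays no part in the primary hypotheses.

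**Conclusion.** The conflict between the blinding claim and the procedure for the blinding test holds, in conditional form. If the people who give the questionnaire also assess outcomes, the claim of blinding to all three groups does not hold for moxibustion versus usual care at weeks 5, 9 and 13. Concealment between moxibustion and sham is not broken by giving the form.

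By design, 64 of 96 participants would be identified directly as not in usual care. That is a count of forms and not an estimate of bias, and the article gives nothing from which bias could be estimated. The bias is likely to be modest for the BFI and could be larger for the MoCA if it is assessor-scored. This should be corrected because the exposed comparison gates the second test and the remedy is cheap. It gives no reason to doubt the sample size, the endpoints or the analysis.

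**What to change.** Change the procedure: have the blinding and credibility forms self-completed, sealed unread, and handed out by existing staff who do not assess outcomes. State in the Blinding section that outcome assessors see neither the forms nor the list of those who received them. If the roles are already separate, one sentence saying so is enough.

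If the roles cannot be separated, restrict the claim in the Abstract, the Blinding section and the Outcome measurements section to assessors blinded between moxibustion and sham only.

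The first option costs a small change of procedure with existing forms. It assumes that each centre has someone other than an outcome assessor to hand them out, and the sealed form keeps answers private if that person is a practitioner. The second option costs a slightly weaker blinding claim. Neither touches the sample size, endpoints or analysis. The trial is recruiting, so the change can protect later participants only, and the report should say from when it applied.

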### Data monitoring and quality control

Data collection will be performed in accordance with the pre-approved protocols, and the quality of the study will be managed by regular monitoring. The monitoring will evaluate whether the recruitment and intervention procedures followed the protocol and that the record of the case report form matches the original document.

To ensure the quality of the study, all researchers should complete a good clinical practice training course. To maintain consistency of the procedures among research centers, we will provide detailed information of every step of this trial to all researchers at the researcher meetings and maintain communication with all researchers throughout the study period. The practitioners will be limited to those who have been licensed as a doctor of Korean medicine by the Ministry of Health and Welfare of South Korea and have a clinical career of 2 or more years.

### Sample size calculation

The primary outcome of this study will be the mean change in average BFI scores from baseline to week 9. Based on a previous study [41], we estimated that the mean difference of the pre- and post-treatment change in the average BFI scores between the moxibustion and sham moxibustion group will be −1.6 and the standard deviation will be 2.0. With a 5% significance level and 80% power, the sample size was calculated to be 25. Considering a 20% drop-out rate, 32 participants are required per group. In conclusion, a total of 96 participants are needed in this trial.

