## Methods/design

### Design

This is a multi-center, three-armed parallel, randomized controlled trial. Ninety-six participants who meet the diagnostic criteria for cancer-related fatigue of the international classification of diseases, tenth revision clinical modification (ICD-10-CM), will be randomly allocated to one of the three groups in a 1:1:1 ratio. One group will be the treatment group (moxibustion group), and the other two will be control groups (sham moxibustion group and usual care group). The flowchart of this trial is shown in Fig. 1.

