### Statistical analysis

An independent statistician blinded to group allocation will perform statistical analysis using SAS® Version 9.4 (SAS institute. Inc., Cary, NC). All statistical analyses will be two-tailed, and the significance level will be set at 5%.

Three types of analysis sets will be used in this study, as follows: intention to treat (ITT) analysis set, full analysis set (FAS), and per-protocol (PP) set. The ITT analysis set will be comprised of the data from every participant who had been randomly assigned to any group in this trial. The FAS set will include the data from all participants who ever received the intervention and provided assessment data at least once following random allocation. The PP set will include only the data from participants who completed the trial without any major violation of the protocol. The FAS will be the primary set for the efficacy analysis, and sensitivity analysis will be conducted to compare the results from the FAS and PP sets. For safety analysis, the ITT set will be the primary set, and the PP set will be used as a supplement. The multiple imputation method will be adopted to handle missing data in incomplete data sets.

Summary statistics of demographic characteristics and baseline measurements of the variables of each group will be presented. Continuous data will be expressed as the mean ± standard deviation, but median and 95% confidence intervals will be provided if necessary. Between-group differences will be analyzed using analysis of variance (ANOVA) or the Kruskal-Wallis test. Categorical data will be presented as frequencies with percentiles and analyzed using the Chi-square test or the Fisher’s exact test.

The primary outcome measure of this study will be the mean change of average BFI scores acquired at baseline and week 9. To validate significant changes in BFI between groups, we assumed two sets of hypotheses.

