**The alternative hypothesis (H**
_**12**_
**):** There is a difference in the mean change of the BFI before and after treatment between the moxibustion group and the sham moxibustion group.

To test the two hypotheses, analysis of covariance (ANCOVA) will be utilized with the baseline BFI value as a covariate and each group as a fixed factor. If any clinically significant difference between groups is identified among the demographic characteristics or the variables measured at baseline, it will be adjusted based on its covariance. The problem of multiple comparison will be solved using the fixed sequence method. In other words, if the H_01_ is rejected and H_11_ is adopted in the statistical test for the first hypothesis set, and then the test for H_02_ will performed. However, when the H_01_ is adoptted, the second hypothesis set for H_02_ will not be verified [42].

The secondary outcome measures of the study will be the mean changes in the BFI, FACT-F, EORTC QLQ C-30 and MoCA before and after the interventions in the three groups. They will be analyzed via the same methods used for the primary outcome measure analysis. Student’s paired t-tests or Wilcoxon signed-rank tests will be used to analyze the differences in the measured values before and after treatment in each group. ANOVA with Dunnett’s post hoc test will be performed to compare the differences in trends per visit. Subgroup analyses will be conducted to check whether there are significant differences in the responses to moxibustion treatment depending on the severity of fatigue, the expected level of treatment, or patterns of cold-heat and deficiency-excess measured at baseline.

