It is known that the placebo effect has a high proportion in the palliative care for the cancer survivors with cancer-related fatigue [45]. It varies by 27–60% depending on the studies [45]. Besides, the sham control interventions of traditional medicine such as moxibustion or acupuncture are not reported to be physiologically inert [46, 47]. Considering the clinical characteristics of the cancer-related fatigue which is sensitive to the placebo response and the unique nature of the sham moxibustion, we cannot rule out the possibility that the difference between the effects of real moxibustion and sham moxibustion will not be statistically significant even though the moxibustion treatment is actually effective because of the placebo effect. This is why we designed a 3-arm parallel study of the usual care group as well as the sham control group.

There are some limitations to this study. First, the outcome measures do not include objective indicators for assessing the level of fatigue. Because fatigue itself is defined as the subjective feeling of the patient, there is currently no way to objectively evaluate it. Some studies have reported that various biomarkers, such as TNF-alpha, interleukin (IL)-1 beta, IL-6, IL-2, CRP, etc., are associated with cancer-related fatigue [6, 10], although the results of these studies are not consistent in regarding this issue. Therefore, there is currently no confirmed biomarker that represents the level of cancer-related fatigue [48]. When definitive biomarkers are discovered in the future, additional clinical trials will need to consider them. Nevertheless, the use of questionnaires to regarding the level of the subjective feelings of fatigue of the subjects is the most widely used method to assess or quantify fatigue as objectively as possible in the field, and we adopted the BFI and FACT-F according to this gold-standard.

Second, there is a limitation pertaining to incomplete blinding. We used moxibustion devices that appeared to be identical in the moxibustion and sham moxibustion groups in an attempt to achieve patient blinding between these two groups. However, it is not possible to blind the participants in the usual care group that do not receive moxibustion treatment. Thus, there could be a concern that this incomplete blinding of participants in the usual care group may introduce bias into the results regarding the outcome measures based on the subjective symptoms that the patients feel.

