However, Atkinson et al. [49] recently showed that there is no clear evidence that the patient blinding is a source of bias in the patient-reported outcome (PRO) or at least that the bias significantly affects the results of the PRO. They insisted that, in clinical trials of therapies for cancer patients, the use of PRO, which is essential for directly assessing the risks, benefits, and value of the therapies to cancer patients, should be promoted regardless of patient blinding because there is no other means that provides information by completely capturing the patient’s experience related to the treatment [49]. Based on such expert opinions, we will adopt a three-armed parallel design, including a usual care group in addition to a sham control group, in this trial even though the primary outcome measure is highly dependent on the patients’ subjectivity.

There is another limitation in terms of patient blinding. The moxibustion delivered to the sham group is designed to not deliver complete warmth to the site of application; therefore, the patients of this group may notice that the treatment is not real moxibustion because it is not sufficiently hot. To prevent this possibility, only patients who have never received moxibustion treatment should be recruited for inclusion. However, this inclusion criterion could significantly lower the recruitment rate. Thus, we decided to register patients regardless of their past experience using moxibustion treatment. To further mitigate this limitation, the real and sham moxibustion devices used in the study will have the same appearance. In addition, the patients will be allowed observe the procedures that the practitioner carries out while operating the moxibustion devices: In case of IM, the participants of both groups will see the smoke and smell the odor from the burning mugwort moxa cone after the practitioner ignites it; and in case of EM, the participants will see the practitioner turn on the EM, which will begin to blink. Finally, we will perform a blinding test to confirm whether patient blinding had been successfully achieved in these two groups.

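### The stated 80% power treats moxibustion versus sham as a stand-alone test, although the fixed sequence allows that test only after a usual-care comparison for which no difference is assumed

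*Protocol article*

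**What the plan says.** The Design section describes three arms; participants "will be randomly allocated to one of the three groups in a 1:1:1 ratio". The Sample size calculation section assumes that the difference in BFI change "between the moxibustion and sham moxibustion group will be −1.6 and the standard deviation will be 2.0". It continues: "With a 5% significance level and 80% power, the sample size was calculated to be 25", and then "Considering a 20% drop-out rate, 32 participants are required per group", which makes 96 in total. No difference or SD is given for moxibustion versus usual care.

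The Statistical analysis section sets two primary hypotheses. H01 is moxibustion versus usual care and H02 is moxibustion versus sham. Both are tested by ANCOVA with baseline BFI as covariate. On sidedness and level: "All statistical analyses will be two-tailed, and the significance level will be set at 5" percent. On multiplicity: "The problem of multiple comparison will be solved using the fixed sequence method". H01 comes first, and if it is not rejected, H02 is not tested.

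The Blinding section accepts that usual-care participants will know their group. The Discussion warns that placebo response may leave the sham comparison non-significant "even though the moxibustion treatment is actually effective because of the placebo effect. This is why we designed a 3-arm parallel study". Read in full, the sentence blames the placebo effect for the non-significance; it does not say that moxibustion works through placebo. The article does not state what may be concluded if H01 is rejected and H02 is not.

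**The concern.** The sizing and the testing order do not match. The trial is sized on the second test in the sequence as if that test were always carried out. The probability of rejecting H02 under a gate is the probability of rejecting H01 and H02 together. On the same inputs this cannot exceed the ungated power, and how far it falls short depends on the usual-care difference, which is not stated.

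Two things are at stake. The first is the power claimed for the only comparison in which both groups of participants are blinded. The second is interpretation. H01 compares 16 attended sessions (twice weekly for 8 weeks) with no sessions, unblinded, on a self-reported score. The Discussion presents the usual-care arm as the answer to a non-significant sham result. Without a stated rule, the result of H01 rejected and H02 not rejected is open to more than one reading.

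**Working it through.** **Inputs from the Protocol article.** Two-sided 5% level; 80% power; difference over sham 1.6; SD 2.0; 25 evaluable per group; 20% drop-out; 1:1:1 allocation; order H01, then H02.

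**Assumption.** The usual-care difference D is not given. I use D from 1.6 to 2.8 with the same SD of 2.0. D = 1.6 means that sham does no better than usual care. Larger values mean a sham response of D − 1.6.

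**Step 1: the article's own figures.**
- n = 2 × (1.960 + 0.842)² × (2.0/1.6)² = 24.5, so 25 per group.
- 25/(1 − 0.20) = 31.25, so 32 per group; 3 × 32 = 96.

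All three figures reproduce.

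**Step 2: ungated power for H02.** SE = 2.0 × √(2/25) = 0.566, and 1.6/0.566 = 2.83. Power = Φ(2.83 − 1.96) = 80.7% by the normal approximation. With a t-test on pooled three-group variance (72 df) it is 79.7%.

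**Step 3: power for H02 under the gate.** The two test statistics share the moxibustion arm, so with equal group sizes their correlation is 0.5. Joint power = P(Z₁ > 1.96 and Z₂ > 1.96), where Z₁ has mean D/0.566 and Z₂ has mean 2.83. The last column is a simulation of three-arm trials with 72 df.

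| D versus usual care | Power of H01 (normal) | Joint power (normal) | Joint power (simulated) |
|---|---|---|---|
| 1.6 | 80.7% | 69.7% | 68–69% |
| 1.8 | 88.9% | 75.1% | 74% |
| 2.0 | 94.2% | 78.2% | 77% |
| 2.4 | 98.9% | 80.4% | 79% |
| 2.8 | 99.9% | 80.7% | 80% |

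The gate costs about 11 points at D = 1.6, about 2.5 to 3 points at 2.0, and less than half a point from 2.4 upwards.

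**Step 4: effect of the ANCOVA.** The sizing uses the SD of the change, but the analysis adjusts for baseline. If change and baseline correlate at 0.3 (assumed; the article gives no value), the residual SD is 2.0 × √(1 − 0.09) = 1.908. By the normal approximation, H02 alone then has 84% power, and joint power is 75% at D = 1.6 and 82% at D = 2.0.

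**Step 5: what H01 can show.** Suppose moxibustion is no better than sham and both are 1.6 points better than usual care. H01 is then rejected in about 80% of trials, and in about 76% H01 is rejected while H02 is not. Those H01 rejections are correct, because a difference from usual care does exist. They say nothing about an effect beyond sham.

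**The case against.** The strongest reply is that the gate probably costs little. The Discussion puts placebo response in this condition at 27–60% and says sham procedures are not inert. If so, sham should beat usual care, D should exceed 1.6, and the 69% row is close to a worst case. H01 also has the same 25 per arm, with about 80%, 94% and 99% power at 1.6, 2.0 and 2.4, so it is wrong to call it underpowered; its power is simply not stated. ANCOVA may bring the joint power back to 80% or more. All of this stands, and it limits the size of the point. It does not supply the missing assumption, and it cuts both ways: the more easily the gate is passed through sham response, the less H01 says about moxibustion itself.

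It can also be said that a full protocol or SAP may hold such detail. But the 80% and the testing order are both printed here, and they do not fit together.

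Two stronger readings are tempting and are not supported. A reader might infer that the article treats rejection of H01 alone as proof of efficacy. It does not say so: the alternative to H01 claims only a difference from usual care, and the fixed sequence controls the type I error over the two primary tests. A reader might also infer that the Discussion contradicts itself when, after reporting a large placebo response, it cites a source for the view that "there is no clear evidence that the patient blinding is a source of bias in the patient-reported outcome". The Discussion first lists incomplete blinding of the usual-care group as a possible source of bias and then reports that view, with a hedge. A disclosed limitation followed by a cited counter-argument is not a contradiction.

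**Conclusion.** The point holds in a limited form. The figures 25, 32 and 96 are arithmetically right, but the 80% describes an ungated test that the plan does not carry out. On the article's change-score inputs, the power for H02 is about 69% to 80% as the usual-care difference goes from 1.6 to 2.4 or more, a loss of between almost nothing and about 11 points. This rests on a common SD of 2.0, 25 evaluable patients per group, and a usual-care difference no smaller than the sham difference, which the article's own placebo argument implies. Baseline adjustment may offset part or all of the loss. The second part is an unstated rule, not a wrong one: the article leaves open what H01 alone would support.

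**What to change.** In the Sample size calculation section:
- State the assumed moxibustion versus usual-care difference and its SD.
- Replace the flat 80% with the joint power for H02 under the fixed sequence, over a plausible range of that difference. On the present inputs this is about 69% at 1.6, 77% at 2.0 and 79–80% from 2.4. If credit is taken for ANCOVA, state the assumed baseline correlation.

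In the Statistical analysis section:
- State that an effect of moxibustion beyond sham is concluded only if H01 and H02 are both rejected.
- State that H01 alone supports only a difference from usual care, including contact and expectation.
- State that the moxibustion versus sham estimate with its 95% CI is reported even if H01 is not rejected.

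The cost is a less favourable stated power and a narrower permitted claim. The change is in wording only; the sample size and the conduct of the trial stay as they are.
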